However, despite their biomechanical effects, few randomised controlled trials have evaluated their clinical efficacy [28-30]. In 156 patients with medial knee OA, no significant effect of laterally wedged insoles on symptoms over 2 years was demonstrated, as compared to control insoles [28]. However, a significant reduction in non-steroidal anti-inflammatory drug intake and greater compliance was observed with laterally wedged insoles, leading the authors to conclude that the results favoured a beneficial effect of the intervention. A recent double-blind, randomized, crossover trial in 90 patients found no effect of 6 weeks of lateral wedge use on pain or [30]. The samples selected for these studies may partly explain the non-significant effect of laterally wedged insoles. Whilst patients demonstrated medial knee OA, selection criteria did not consider knee joint alignment. Significant effects are more likely in participants with evidence of varus malalignment, rather than in a diverse cohort where alignment is likely to range from valgus (in which lateral wedges could be detrimental) to neutral to varus.

As previously stated, it is also important to evaluate the effect of treatment on disease progression. Only one clinical trial has investigated the effect of lateral wedges on knee OA progression [29]. Using annual x-rays for two years, this study failed to show that lateral wedges slowed joint space narrowing over time compared to control insoles. This non-significant finding may relate to the use of relatively insensitive x-rays as a measure of disease progression, as well as to an inappropriate patient group and the use of a short rather than full length wedge. Given the paucity of data attesting to the structural effects of lateral wedges over time, further research is necessary using more sensitive methods of measuring disease progression such as magnetic resonance imaging. Furthermore, no study to date has evaluated the cost-effectiveness of lateral wedges.

The aim of this trial is to determine whether wearing lateral wedge insoles for 12 months improves pain, physical function and health-related quality of life, slows structural disease progression and is more cost-effective than control flat insoles in individuals with medial knee joint OA and varus malalignment.

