Knee cartilage volume will be measured using magnetic resonance imaging (MRI). Knees will be imaged in a sagittal plane on a 1.5-T whole-body magnetic resonance unit (Signa Advantage HiSpeed GEMedical Systems, Milwaukee, WI, USA) using a commercial receive-only extremity coil. The following sequence and parameters will be used: a T_1_-weighted, fat-suppressed 3D gradient recall acquisition in the steady state; flip angle 55 degrees; repetition time 58 ms; echo time 12 ms; field of view 16 cm; 60 partitions; 512 (frequency direction, superior-inferior) × 512 (phase encoding direction, anterior-posterior) matrix; one acquisition, time 11 min 56 sec. Sagittal images will be obtained at a partition thickness of 1.5 mm and an in-plane resolution of 0.31 mm × 0.31 mm (512 × 512 pixels) [37]. Knee cartilage volume will be determined by a blinded assessor analyzing baseline and final MRI pairs. 3D image processing will be performed using the software program OSIRIS (University of Geneva). In this technique, the image data will be transferred to a workstation and an isotropic voxel size will then be obtained by a trilinear interpolation routine. The volume of individual cartilage plates will be isolated from the total volume by manually drawing disarticulation contours around the cartilage boundaries on a section-by-section basis. These data will then be resampled by means of bilinear and cubic interpolation (area of 312 × 312 μm and 1.5 mm thickness, continuous sections) for the final 3D rendering. The volume of the particular cartilage plate will then be determined by summing all the pertinent voxels within the resultant binary volume. The CV of this method in our hands is 2% [37]. Knee cartilage volume will be measured for both the medial and lateral tibial compartments but the primary outcome will be the change in medial tibial cartilage volume. Bone size is a significant determinant of knee cartilage volume and thus a potential confounder [38]. Medial and lateral tibial plateaux areas as a measure of bone size will determined by creating an isotropic volume from the sagittal, T1-weighted fat saturation images, described above. This data will be reformatted in the axial plane and the area directly measured from these images as previously described [19]. The CV for the tibial plateau areas is 2.3% [19].

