### Sample size calculations

Our sample size of 200 ensures adequate power for the two principal endpoints of change in pain and change in knee cartilage volume. Assuming that lateral wedges result in a mean pain reduction of 2 on our numeric rating scale (the minimum clinically important difference to be detected in OA trials [49]), that control insoles have a small placebo effect of 0.5 and that there is a SD of change of 3 (based on our previous data evaluating conservative OA interventions [50,51]), 170 participants would be required in total to give 80% power (2 sided test, alpha = 0.05). We have previously demonstrated a reduction in pain of this magnitude with knee taping [50] and physiotherapy for knee OA [51].

The other major end point is rate of knee cartilage loss. We have previously shown that the rate of tibial cartilage loss is 5.3 +/- 5.2% per year in a cohort with knee OA [52]. We categorized OA participants into tertiles: cartilage loss <3% per annum, 3–8% per annum and > 8% per annum. We found a linear increase in the risk of undergoing a knee replacement within 4 years [53]. Participants who lost cartilage at the rate of 3–8% per annum had a 2.4 fold (0.4 to 12.2) increased risk of requiring a knee replacement compared to participants who lost cartilage at the rate of <3% per annum. Those with the highest rate of loss of knee cartilage (>8% per annum) had a 7.1 fold (1.4 to 36.5) increased risk of requiring a knee replacement. These data suggest that a clinically useful outcome with lateral wedges would be to reduce the rate of knee cartilage loss to <3% per annum. With 100 subjects in each arm of the study, we will have 80% power to show a difference between a 5.3 +/- 5.2% per year rate of cartilage loss in the control group [52] and a <3% rate of cartilage loss in the intervention group (2 sided test, alpha = 0.05). This also takes into account a 20% drop-out rate.

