### Statistical analysis

A blinded statistician will analyse the data. All analyses will be conducted on an intention-to-treat principle using all randomized participants. Missing data will be replaced by the last score carried forward. Demographic characteristics and baseline data will be summarised by descriptive statistics. For outcomes measured using an essentially continuous scale, differences in mean change from baseline to 12 months will be compared between groups using linear regression modelling adjusting for baseline levels of the outcome measure. For knee cartilage volume, bone area, age and gender will also be included as covariates [54,55]. Model assumptions will be checked by standard diagnostic plots [56]. Participant measures of perceived improvement following lateral wedges or flat insole treatments will be compared by calculating the relative risks and their 95% confidence intervals using log binomial regression [57].

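### Carrying the last score forward assigns zero cartilage loss to anyone without a 12-month MRI, which shrinks the structural effect (80% stated power becomes about 75%) and can bias it either way if drop-out differs by arm

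*Protocol article*

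**What the plan says.** The Statistical analysis section applies intention-to-treat to all randomised participants and gives one rule for missing values: "Missing data will be replaced by the last score carried forward". It makes no exception for MRI. Change from baseline to 12 months is compared by linear regression adjusted for baseline, with bone area, age and gender added for cartilage volume.

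The Outcome assessment section sets two assessments, at baseline and at 12 months. Its MRI paragraph says: "Knee cartilage volume will be determined by a blinded assessor analyzing baseline and final MRI pairs". No interim scan is described.

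The Sample size calculations section takes from earlier work that the "rate of tibial cartilage loss is 5.3 +/- 5.2% per year in a cohort with knee OA [52"]. For 100 per arm it then says "we will have 80% power to show a difference between a 5.3 +/- 5.2% per year rate of cartilage loss in the control group" and "a <3% rate of cartilage loss in the intervention group" ("2 sided test, alpha = 0.05"), and adds: "This also takes into account a 20% drop-out rate".

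**The concern.** Carry-forward needs a post-baseline value to carry. With two time points there is none, so the rule becomes baseline carried forward and the imputed change is zero. On a measure expected to worsen in both arms, zero is not a neutral value: it is better than the mean planned for the treated arm. Each missing scan is scored as a structural success in whichever arm it falls, and the regression treats it as an observed value.

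Two things are at stake. First, even with equal drop-out the estimated effect is diluted, so the power figure no longer describes the analysis that is specified. Second, if the arms lose different numbers of scans, part of the estimated difference comes from the imputation and not from the insoles. This could create a structural benefit, hide one or exaggerate one.

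**Working it through.** **Inputs.** From Sample size calculations: control mean loss 5.3% per year, SD 5.2, wedge mean below 3%, 100 per arm, 20% drop-out, two-sided alpha 0.05. Assumptions: wedge mean exactly 3.0, SD 5.2 in both arms, missingness unrelated to loss within arm, and no precision gain from covariates (the protocol gives no correlation).

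**Step 1: reproduce the stated 80%.** With 80 observed per arm, SE = 5.2 × √(2/80) = 0.822 and z = 2.30/0.822 = 2.80. Power = Φ(2.80 − 1.96) = 79.9%. With 100 per arm and nobody missing, power is 87.9%. So the stated figure fits a calculation in which drop-outs are absent from the analysis.

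**Step 2: the rule as written.** If a share d of an arm with mean loss μ is set to zero:

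- arm mean = (1 − d)μ
- arm variance = (1 − d) × 5.2² + d(1 − d)μ²

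With d = 0.20 in both arms:

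- control: mean 0.8 × 5.3 = 4.24, SD 5.11
- wedge: mean 0.8 × 3.0 = 2.40, SD 4.80
- difference 1.84, SE = √((5.11² + 4.80²)/100) = 0.701, z = 2.62, power 74.6%

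Simulated t-tests gave 74.3% with random drop-out and 75.7% with exactly 20 missing per arm. For other equal rates, the formula gives 81.9% at 10% drop-out, 78.4% at 15%, 70.6% at 25% and 66.4% at 30%.

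**Step 3: unequal drop-out.** The bias in the difference (control loss minus wedge loss) is d_wedge × μ_wedge − d_control × μ_control. The splits below are assumed, and all average 20%.

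| Drop-out, control / wedge | No true effect (5.3 in both arms): spurious difference | Type I error | Planned effect (true 2.30): expected difference | Power |
|---|---|---|---|---|
| 20% / 20% | 0 | 5% | 1.84 | 75% |
| 18% / 22% | +0.21 | 6% | – | – |
| 15% / 25% | +0.53 | 11% | 2.26 | 90% |
| 25% / 15% | −0.53 | 11% | 1.43 | 53% |
| 10% / 30% | +1.06 | 31% | 2.67 | 97% |

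Positive values favour wedges. With the numbers missing held fixed, simulation gave type I errors of 9% (15%/25%) and 30% (10%/30%).

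Under the planned effect the bias is zero when d_wedge/d_control = 5.3/3.0 = 1.77, for example about 14.5% control and 25.5% wedge. With no true effect, any imbalance produces bias.

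**Step 4: pain.** The planned means are reductions of 2 and 0.5, SD 3. With 20% zeros in each arm the difference falls from 1.5 to 0.8 × 1.5 = 1.2. SE is 0.388 and power about 87%, still above the 80% planned for that outcome.

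**The case against.** **The target is below 3%, not equal to 3%.** With a wedge mean of 2.85%, carry-forward at 20% drop-out gives 79.9% power. The arithmetic is right, but the comparison is not like for like: the same 2.85% raises power for 80 observed per arm to about 85%. The loss of about five points remains.

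**The protocol does not say how drop-out entered the calculation.** That is so. The figure of 80 observed per arm is inferred because it reproduces 80%. The mismatch is one of about five power points, so it would be too strong to say that the sample size is invalid.

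**Unequal drop-out is not in the documents.** This also stands. Only an overall 20% is given, and a modest 18%/22% split moves type I error only to about 6%. A reader might take the Background remark that "greater compliance was observed with laterally wedged insoles" as evidence of unequal attrition here. It concerns insole wear in another trial, and a participant who stops wearing insoles can still be scanned. A reader might also infer that the arm losing more people always gains against the truth. The 15%/25% row shows otherwise: under the planned effect that estimate is almost unbiased.

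**Scans are read in pairs, so a lone baseline scan may never be read.** If so, there is no volume to carry, and the rule cannot be applied to this outcome at all. Either reading calls for a change in the text.

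**Knee replacement.** One might argue that fast losers have the knee replaced and are then scored as zero. The cited risks are over 4 years with wide intervals (0.4 to 12.2 and 1.4 to 36.5), and no 12-month rate is given. The point does not rest on this.

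**The analysis plan may settle it.** An unseen plan could replace the rule, but the protocol does not leave the matter open: it fixes carry-forward explicitly.

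**Conclusion.** The concern holds. As written, the rule scores every missing final MRI as zero loss on a primary outcome that is expected to worsen. At the protocol's own 20% drop-out, equal by arm, the effect is diluted by one fifth (2.30 to 1.84 points) and power is about 75% against the stated 80%. This rests on a wedge mean of 3.0, SD 5.2 in both arms and drop-out unrelated to loss.

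If drop-out differs by arm, bias can go in either direction. The type I errors of 6%, 11% and 31% illustrate assumed splits and do not forecast this trial. The documents do not support the stronger reading that bias arises whenever drop-out differs and only then: under the planned effect it cancels at one ratio and is present when drop-out is equal. For pain, the rule dilutes the estimate but does not threaten the planned power.

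**What to change.** 1. Remove carry-forward for cartilage volume, and preferably for the other continuous outcomes measured only at baseline and 12 months.
2. State that the 12-month assessment already planned, including MRI, is sought from every randomised participant whether or not they still wear the insoles.
3. Fit the planned baseline-adjusted regression to observed data, or after multiple imputation within arm using covariates already collected (baseline volume, bone area, age, gender, Kellgren and Lawrence grade, log-book wear and discomfort).
4. Add a delta-shift sensitivity analysis in which missing scans carry a loss, varied separately by arm.
5. If carry-forward is kept, restate the cartilage power as about 75% at 20% drop-out.

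The cost is revised wording and some programming, with no extra participants or planned visits. The main analysis would then rest on a missing-at-random assumption, which the delta-shift analysis probes, and intervals would be somewhat wider than with zeros treated as data.

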**Methods/Design:**

Two hundred participants with painful radiographic medial knee OA and varus malalignment will be recruited from the community and randomly allocated to lateral wedge or control insole groups using concealed allocation. Participants will be blinded as to which insole is considered therapeutic. Blinded follow up assessment will be conducted at 12 months after randomisation. The outcome measures are valid and reliable measures recommended for OA clinical trials. Questionnaires will assess changes in pain, physical function and health-related quality-of-life. Magnetic resonance imaging will measure changes in tibial cartilage volume. To evaluate cost-effectiveness, participants will record the use of all health-related treatments in a log-book returned to the assessor on a monthly basis. To test the effect of the intervention using an intention-to-treat analysis, linear regression modelling will be applied adjusting for baseline outcome values and other demographic characteristics.

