## Methods/Design

### Design

This will be a double-blind randomised controlled trial (Figure 1). Potential participants will undergo telephone screening followed by clinical examination by a physiotherapist or medical practitioner and a podiatrist to ensure they fulfil selection criteria. A screening x-ray will be performed to assess knee joint alignment and disease severity. Eligible participants will then be stratified by disease severity (Kellgren and Lawrence grade 2 and 3 [31] and randomly allocated in permuted blocks of 6 to 12 to lateral wedge or control flat insoles groups. The randomisation sequence will be generated *a priori *using the random number function in Excel by an independent investigator not directly involved in assessment of participants. Allocation will be sealed in opaque and consecutively numbered envelopes held in a central location. These will be opened in sequence by a person not involved in the study after recruitment and baseline testing of participants.

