### Outcome assessment

Participants will be assessed at baseline and at 12 months by an assessor blinded to group allocation. Outcome measures have been selected based on those recommended for clinical trials of knee OA [35,36]. In those with bilateral knee OA, only the most symptomatic knee will be assessed.

Age, gender, duration of knee OA symptoms, previous treatment, surgery and medication use for knee OA will be obtained by questionnaire. Radiographic disease severity will be assessed from the baseline x-ray using the Kellgren and Lawrence grading system [31]. Skyline knee x-rays performed in nonweightbearing at 20° knee flexion will also be obtained to assess severity of OA within the patellofemoral joint. X-rays will be evaluated according to osteophytes and joint space narrowing based on a 4 point scale [34].

The primary outcomes will be knee pain and knee cartilage volume (Table 1). Average knee pain in the past week will be self-assessed by an 11-point horizontal numeric rating scale with terminal descriptors of zero = no pain and 10 = worst pain possible. Such measurement has demonstrated reliability in OA [35].

**Table 1 T1:** Outcome measures

**Primary Outcomes**	**Measurement**
Average pain in the past week	11 point horizontal numeric rating scale (end descriptors of 0 = no pain and 10 = worst pain possible)
Medial tibial compartment cartilage volume	Magnetic resonance imaging

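### Randomisation is stratified by Kellgren-Lawrence grade, but the planned linear models leave the stratum out; the tests are then slightly conservative if grade is prognostic

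*Protocol article*

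**What the plan says.** **Allocation.** Protocol article, Design: "Eligible participants will then be stratified by disease severity (Kellgren and Lawrence grade 2 and 3" and then "randomly allocated in permuted blocks of 6 to 12 to lateral wedge or control flat insoles groups". KL grade is the only stratification factor named.

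**Analysis.** Protocol article, Statistical analysis: change from baseline to 12 months in continuous outcomes is compared "using linear regression modelling adjusting for baseline levels of the outcome measure". One outcome receives more: "For knee cartilage volume, bone area, age and gender will also be included as covariates".

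**Endpoints affected.** Outcome assessment: "The primary outcomes will be knee pain and knee cartilage volume". The planned models are therefore:

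- pain: baseline pain only;
- cartilage: baseline volume, bone area, age and gender.

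**Abstract.** Its Methods/Design paragraph summarises the analysis as "linear regression modelling will be applied adjusting for baseline outcome values and other demographic characteristics", without naming the characteristics or the outcomes concerned.

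**The concern.** Stratified blocking forces the arms to be nearly balanced on KL grade. If grade predicts outcome, that balance reduces the true sampling variance of the treatment difference. A model without grade cannot see the reduction. The between-grade variation stays in the residual, so the printed standard error is larger than the real one. Confidence intervals come out too wide and tests reject less often than their nominal level.

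The cartilage endpoint is the one to watch, because its planned power is only just 80% after drop-out.

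There is also a smaller wording problem. The abstract mentions demographic adjustment in general, whereas the Methods plan none for pain. The two descriptions of the pain model do not match.

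**Working it through.** **Inputs from the protocol article (Sample size calculations).** Cartilage loss is 5.3% per year (SD 5.2) in the control arm and below 3% in the wedge arm, taken here as 3%, so the difference is 5.3 − 3 = 2.3. There are 100 per arm with 20% drop-out, so 80 evaluable per arm. The test is two-sided with alpha 0.05.

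**Assumption, not in the documents.** R² is the share of residual outcome variance that KL grade explains after the planned covariates. The range used is 0, 2%, 5% and 10%, with arms balanced within grade.

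**Step 1: reproduce the stated power.** SE = 5.2 × √(2/80) = 0.822. The standardised difference is 2.3/0.822 = 2.797. Power = Φ(2.797 − 1.96) = Φ(0.837) = 79.9% (79.4% with the t distribution). The stated 80% reproduces.

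**Step 2: size of the standard error.** With balance within grade, the true standard error is SE × √(1 − R²), while the model without grade reports SE. The inflation factor is 1/√(1 − R²).

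**Step 3: type I error without KL.** 2 × [1 − Φ(1.96/√(1 − R²))].

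**Step 4: power with and without KL, like for like.** Stratification has already reduced the true variance in both analyses, so:

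- without KL: Φ((2.797 − 1.96)/√(1 − R²));
- with KL: Φ(2.797/√(1 − R²) − 1.96).

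| Assumed R² | SE inflation | Type I error without KL | Cartilage power without KL | Cartilage power with KL | Gain (points) |
|---|---|---|---|---|---|
| 0 | 0 | 5.0% | 79.9% | 79.9% | 0 |
| 2% | 1.0% | 4.8% | Φ(0.846) = 80.1% | Φ(0.866) = 80.7% | about 0.5 |
| 5% | 2.6% | 4.4% | Φ(0.859) = 80.5% | Φ(0.910) = 81.9% | about 1.4 |
| 10% | 5.4% | 3.9% | Φ(0.883) = 81.1% | Φ(0.989) = 83.9% | about 2.7 |

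**Step 5: check by simulation.** This used 20,000 replicates, 80 per arm and two equal strata balanced by arm. Cartilage power without and with the stratum was 79.0% and 79.0% at R² = 0, 79.8% and 81.1% at 5%, and 80.4% and 83.1% at 10%. Type I error without the stratum was 5.0%, 4.3% and 4.0%; with it, it stayed near 5%. These agree with the formulas within simulation error.

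**Step 6: pain.** "lateral wedges result in a mean pain reduction of 2 on our numeric rating scale", with 0.5 in the control arm and SD of change 3, gives a difference of 1.5. At 80 per arm the simulated power without and with the stratum was 88.9% and 89.9% at R² = 5%, and 89.3% and 91.1% at 10%. The gain is about 1 to 2 points.

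**Step 7: the covariate descriptions compared.** For cartilage, the abstract is a loose paraphrase of age and gender that does not mention bone area. For pain, the Methods list no demographic covariate, so the abstract does not match.

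**The case against.** **An article may leave handling of strata to a fuller plan.** Often true, but this article does not stay silent on covariates. It gives a specific list for each primary outcome, and the list omits the one factor the design balances on. Naming that factor improves something the article has already fixed.

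**The loss may be nil.** This stands. What counts is variance explained beyond the planned covariates, and the documents give no value. If it is zero, nothing is lost. The figures also assume exact balance within grade, which incomplete blocks and drop-out would loosen.

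**The cartilage endpoint may have some slack.** This stands in part. The SD of 5.2 is a cohort figure, the planned covariates may reduce it, and 2.3 is the smallest difference consistent with a target below 3%.

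**Stronger readings to avoid.**

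- A reader might infer that the primary models are not fixed. They are: the Statistical analysis section states the covariates for each primary outcome, and the abstract is a condensed sentence that specifies no rival pain model. Nor does the abstract say that every outcome is adjusted for demographic characteristics.
- A reader might credit the KL term with more power by setting the with-KL figures against the 79% to 80% that applies at R² = 0. That ignores the variance reduction stratification already gives the unadjusted analysis.
- A reader might extend the KL term to the log-binomial and the cost and QALY analyses. The article does not support that. Its cost-effectiveness intervals come from bootstrapping, regression for the acceptability curve is conditional on baseline imbalance, and log-binomial models can fail to converge as covariates are added.

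**Conclusion.** The point holds in a limited form. The linear models omit the stratification factor. If KL grade is prognostic beyond the planned covariates, standard errors are overstated by 1.0% to 5.4% and actual type I error falls to between 4.8% and 3.9%, over an assumed R² of 2% to 10%. Including the stratum would then restore the nominal level and add about 0.5 to 2.7 points of cartilage power at 80 per arm. At R² = 0 the effect is nil. The planned tests remain valid: the treatment estimate is unbiased and the false-positive rate is not raised. The abstract mismatch is a wording matter and a real discrepancy only for pain.

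**What to change.** Add KL grade (2 versus 3) as a covariate to the linear regression models for the continuous outcomes. For the two primary outcomes:

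- pain: baseline pain + KL grade;
- cartilage: baseline volume + bone area + age + gender + KL grade.

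Reword the abstract so that demographic covariates are tied to cartilage volume, in line with the Statistical analysis section.

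The cost is a change of wording and one degree of freedom per model. KL grade is already taken from the baseline x-ray, so no new data are needed.

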Recent research has found that a higher adduction moment is associated with more severe knee pain [14] and greater radiographic disease severity [15]. Severity of knee malalignment is also significantly associated with knee pain severity and physical function [16]. Longitudinal studies have demonstrated that as little as a one-unit increase in the adduction moment is associated with up to a 6.5-fold increase in the risk of disease progression [14,17]. Similarly, knee joint varus malalignment is also correlated with disease progression [16,18,19]. Given the importance of the knee adduction moment and joint alignment with regard to both symptom severity and disease progression in knee OA, conservative strategies to alter these biomechanical factors constitute a logical rehabilitative approach.

In 1987, Sasaki and Yasuda [20,21] first reported the potential of a laterally wedged insole in the shoe to treat medial knee OA. They demonstrated that the insole statically aligned the knee in a more upright position by shifting the calcaneus into a valgus position relative to the tibia. The authors concluded that such an alteration helped reduce excessive loading of the medial joint surface, leading to mitigation of knee pain. Biomechanical studies have since evaluated the effects of laterally wedged insoles on knee alignment and medial compartment loading. Ogata et al [22] demonstrated that lateral thrust of the knee (which forces the knee into varus alignment) was reduced with lateral wedges in people with normal and osteoarthritic knees. Similar results have been reported by more recent studies [23-25], with Kerrigan et al [24] demonstrating that a 5° laterally wedged insole significantly reduces the knee adduction moment by 6% in medial knee OA. Finally, Giffin et al [26] observed a significant varus to valgus shift in knee alignment on static radiographs with a lateral heel wedge although this has not been a consistent finding [27]. Thus there is evidence that lateral wedges can reduce varus malalignment and the adduction moment, two key biomechanical features that are associated with knee OA symptoms and disease progression.

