### Participants

Two hundred men and women aged over 50 years will be recruited from the community via advertisements in local clubs, libraries, and the print and radio media in metropolitan Melbourne, Australia. Eligibility will be confirmed by radiographic and clinical examination. People with tibiofemoral joint OA fulfilling American College of Rheumatology classification criteria [32] and reporting average knee pain on walking >3 on an 11-point scale will be included. Other inclusion criteria will be: (i) knee alignment ≤185° on a standardised semiflexed standing posteroanterior knee x-ray (which corresponds to a mechanical axis of ≤180° on a full leg xray indicating varus malalignment) [33]; (ii) predominance of pain/tenderness over the medial region of the knee and; (iii) medial radiographic OA defined as at least Grade 1 medial joint space narrowing or Grade 1 medial tibial or femoral osteophytes [34].

The exclusion criteria will include: (i) questionable or advanced radiographic knee OA (Kellgren and Lawrence stages 1 and 4 [31]); (ii) predominant patellofemoral joint symptoms based on clinical examination; (iii) knee surgery or intra-articular corticosteroid injection within 6 months; (iv) current or past (within 4 weeks) oral corticosteroid use; (v) systemic arthritic conditions; (vi) history of tibiofemoral/patellofemoral joint replacement or tibial osteotomy; (vii) any other muscular, joint or neurological condition affecting lower limb function; (viii) ankle/foot pathology or pain that precludes the use of insoles; (ix) use of foot orthotics within past 6 months; (x) regular use of footwear that does not accommodate an insole; (xi) contraindications to magnetic resonance imaging (eg. metal implant, cochlear implant, claustrophobia, pacemaker); (xii) planning to commence exercise or other treatment for knee OA in the next 12 months; (xiii) regular use of a gait aid and; (xiv) non-English speaking.

Ethical approval has been obtained from the University of Melbourne Human Research Ethics Committee (HREC No. 050031) and from the Department of Human Services Victoria, Radiation Safety Committee. All participants will provide written informed consent.

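### The cartilage model leaves out baseline knee alignment, a measured predictor of progression by the protocol's own account; adding it would be a free but probably small gain in precision

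*Protocol article*

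**What the plan says.** The Statistical analysis section of the protocol article compares change in continuous outcomes by "linear regression modelling adjusting for baseline levels of the outcome measure". For the cartilage outcome it extends the list: "For knee cartilage volume, bone area, age and gender will also be included as covariates". The main model for change in medial tibial cartilage volume therefore has four baseline covariates, and alignment is not one of them.

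Elsewhere the article treats alignment as prognostic and has it measured:

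- Background: "knee joint varus malalignment is also correlated with disease progression".
- Discussion: subgroups of knee OA defined by local factors such as malalignment are said to differ in their risk of progression.
- Design: "A screening x-ray will be performed to assess knee joint alignment and disease severity".
- Participants: entry requires "knee alignment ≤185° on a standardised semiflexed standing posteroanterior knee x-ray".

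Randomisation is stratified by Kellgren and Lawrence grade, not by alignment.

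**The concern.** In a randomised comparison, a baseline covariate earns its place by predicting the analysed outcome, which here is change in cartilage volume. The outcome assessment section justifies bone area as a determinant of cartilage volume, that is, of level. The variable that the article itself connects with progression is alignment. It should be on file for everyone because it decides eligibility, but it enters no stated model.

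At stake is the width of the interval for one of two primary outcomes. The cartilage sample size has little margin over 80% power, so even a small gain is worth taking if it is free. A term named in advance also settles how a visible baseline difference in alignment is handled. The same term added after the baseline table has been seen would carry less weight.

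**Working it through.** **Inputs from Sample size calculations.** The control arm is given as "5.3 +/- 5.2% per year rate of cartilage loss in the control group" and the wedge arm as below 3%, taken here as 3%. The difference is therefore 5.3 − 3 = 2.3 points. The SD of 5.2 is applied to both arms. There are 100 per arm with 20% drop-out, so 80 evaluable per arm; alpha is 0.05, two-sided.

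**Step 1: reproduce the stated power without alignment.**

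- SE = 5.2 × √(2/80) = 0.822.
- Power = Φ(2.3/0.822 − 1.96) = Φ(0.84) = 79.9%; noncentral t gives 79.4%.
- In the other direction, 80% power needs 81 per arm, and 81/0.8 rounds up to 102, against 100 planned.

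The stated 80% holds and relies on no covariate.

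**Step 2: add alignment.** The article gives no correlation between alignment and 12-month change, so a partial correlation r is assumed. Residual SD = 5.2 × √(1 − r²), and SE = residual SD × √(2/80).

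| Assumed r | Residual SD | SE | Fall in SE | Power, normal | Power, noncentral t |
|---|---|---|---|---|---|
| 0 | 5.200 | 0.822 | none | 79.9% | 79.4% |
| 0.1 | 5.174 | 0.818 | 0.5% | 80.3% | 79.8% |
| 0.2 | 5.095 | 0.806 | 2.0% | 81.5% | 81.0% |
| 0.3 | 4.960 | 0.784 | 4.6% | 83.5% | 83.0% |

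The percentage fall in SE holds whatever the four planned covariates explain. The power columns take them to explain nothing, so they illustrate the gain and do not forecast power.

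**Step 3: allow for the entry limit.** Restricting entry to 185° or less narrows the spread of alignment and weakens its correlation with loss. If eligibility cuts the SD of alignment to a fraction u of its unrestricted value, a correlation R becomes R·u/√(1 − R² + R²u²). With R = 0.3:

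- u = 0.5: 0.15/√(0.91 + 0.0225) = 0.155.
- u = 0.8: 0.24/√(0.91 + 0.0576) = 0.244.

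R-squared is then about 2% to 6%, and the SE falls by about 1% to 3%. Both R and u are assumptions.

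**Step 4: size of a chance imbalance.** A one-standard-error imbalance in alignment is √(2/80) = 0.158 SD. At r = 0.3 it moves the unadjusted difference by 0.3 × 5.2 × 0.158 = 0.25 points. That is 0.25/0.822 = 0.3 standard errors.

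**Step 5: price of the term.** The planned model estimates six coefficients (intercept, group, baseline volume, bone area, age, gender). With 160 evaluable participants, 160 − 6 = 154 residual degrees of freedom remain; alignment takes one.

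**The case against.** The strongest reply is that nothing here is an error. The planned model is valid, fixed in advance and supported by citations. Leaving a prognostic covariate out of a randomised linear model biases nothing and does not harm the type I error. No section promises adjustment for alignment. All of this stands, and it limits the point to an optional improvement.

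A reader might go further and infer that the omission wastes substantial precision, that chance imbalance in alignment distorts the structural result, or that the cartilage endpoint is underpowered. The article supports none of these:

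- **Precision.** The article gives no strength of association. It speaks of progression in general, not of 12-month MRI volume change in a varus-only sample of grade 2 and 3 knees. One source cited for alignment and progression is also cited for the MRI plateau-area method. That hints at relevance but supplies no coefficient.
- **Imbalance.** The 0.25-point shift is about 11% of the 2.3-point target, which can look like bias. It is only 0.3 standard errors, and the confidence interval already allows for chance imbalance of this kind. The Background says that alignment becomes varus as the medial space narrows, so stratifying by grade may partly balance alignment too. Baseline volume may absorb more.
- **Power.** The 80% was derived from the unadjusted SD and takes no credit for any covariate.

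It also cannot be shown that the listed covariates are the less relevant ones. The article explains only bone size as a determinant of volume. The rationale for age and gender rests on cited work that is not at hand.

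What survives is narrow. The protocol names a prognostic variable, collects it on everyone and leaves it out of a model whose covariates it lists. The entry limit is one-sided, so some variation within varus knees remains to be used.

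**Conclusion.** The point holds as a low-priority improvement. The cartilage model omits a baseline variable that the protocol itself links to progression and assesses in every participant. There is no bias, and the stated 80% power is not invalidated. The likely loss is small: about 0.5% to 5% of the standard error for an assumed partial correlation of 0.1 to 0.3, or power of about 80% to 83% in place of 79-80%. The lower end is more likely because of the entry limit.

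This rests on the assumed correlation, on a linear relation between angle and loss, on the sample size SD of 5.2 serving as the residual SD, and on the screening angle being recorded as a number.

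**What to change.** Before unblinding, add the screening alignment angle of the study knee, in degrees and as a single continuous linear term, to the cartilage model beside baseline volume, bone area, age and gender. In participants with bilateral disease, use the angle of the knee that is assessed for outcome.

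The cost is one named covariate and one of about 154 residual degrees of freedom. It needs no new measurement and no change to the sample size. Missing values should not arise, because the angle decides eligibility.
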